#### Exclusion criteria

Participants meeting any of the following criteria were excluded: (1) low back pain secondary to diagnosed internal medical conditions or previous lumbar spine surgery, confirmed by relevant laboratory and imaging examinations; (2) patients with severe osteoporosis, spinal fractures, inflammatory spondyloarthritis (such as ankylosing spondylitis), spondylolisthesis, lumbar spinal stenosis, and lumbar disc herniation; (3) presence of severe cardiac, pulmonary, hepatic, or renal insufficiency or significant impairment, or coagulation disorders, or history of active peptic ulcer, severe gastrointestinal bleeding, active inflammatory bowel disease, and aspirin-induced asthma; (4) inability to comply with the study protocol due to severe psychiatric illness or cognitive impairment; (5) known allergy to non-steroidal anti-inflammatory drugs (NSAIDs), alcohol, or electrode pads, or patients taking medications that severely interact with NSAIDs like Loxoprofen, such as anticoagulants and antiplatelets, lithium or methotrexate, and SSRIs; (6) women who were pregnant or breastfeeding.

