#### Experimental group

The experimental group received Tuina combined with the Loxoprofen Sodium patch. The Tuina intervention will be performed by a physician with over 10 years of experience in Tuina treatment from the Department of Tuina, the Affiliated Rehabilitation Hospital of Fujian University of Traditional Chinese Medicine. The patient is first guided to assume a prone position. The Tuina therapist sequentially applies the rolling manipulation and palmar pressing-kneading manipulation to the Bladder Meridian on both sides of the lower back and the posterolateral aspect of the affected lower limb. Each region is treated for 5 min, totaling 10 min, to alleviate muscle tension. Maintaining the same position, finger-pressing manipulation is applied to the acupoints of Ashi, BL23 (Shenshu), GV4 (Mingmen), BL25 (Dachangshu), BL26 (Guanyuanshu), BL54 (Zhibian), GB30 (Huantiao), BL40 (Weizhong): (see Figure 2 and Table 1), with force generated from the forearm and fingers. The intensity is adjusted to the patient’s comfort level, and rhythmic pressing and kneading are performed for 5 min. The patient is then guided to a lateral recumbent position. The Tuina therapist first applies thumb-plucking manipulation to the bilateral erector spine muscles for 3 to 5 repetitions, followed by lumbar oblique-pulling manipulation once on each side, until the audible sound of bubbles (“click” sound) in the joint cavity can be heard at the end of the operation. Subsequently, the patient returns to the prone position, and the bilateral sacrospinal muscles are patted, followed by tapping on the lumbosacral region to relieve spasm, alleviate pain, and relax the sinews and unblock the meridians. The intervention is administered three times weekly, with each session lasting 30 min, for a continuous treatment duration of 4 weeks.

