#### Secondary outcomes

Secondary outcome measures included ODI questionnaire, SF-36, BDI-II, BAI, sEMG, MSK US, and medication usage.

ODI Questionnaire (22, 23): This questionnaire is considered a standard measure for all LBP. It evaluates various aspects, including the intensity of low back and leg pain, daily activities, and social life. The ODI 2.0 version will be used in this trial, as it is the most commonly employed version in low back pain research and has well-established psychometric properties. The ODI score ranges from 0 to 100%. The final score is inversely related to the level of lumbar function; a higher index indicates more severe dysfunction, whereas a lower index suggests milder dysfunction.SF-36 (24): The full version of the SF-36 is a widely used generic health assessment tool. Its physical health component comprises four domains: Physical Functioning (assessing capacity for daily activities), Role-Physical (reflecting the impact of health problems on work or daily life), Bodily Pain (quantifying pain intensity and its interference), and General Health Perceptions (evaluating the individual’s overall view of their health). The standard (4-week recall) version will be administered, as it is appropriate for chronic conditions where stable health status over the past month is of interest. Scores for each item are transformed using a standardized algorithm to a 0–100 scale, with higher scores indicating better physical health status.BDI-II (1): This is a self-report inventory used to assess the severity of depressive symptoms over a 2-week recall period. It contains 21 items covering emotional, cognitive, and somatic symptoms, such as hopelessness, self-blame, and sleep disturbances. Each item is rated on a 0–3 scale, yielding a total score range of 0–63. Higher scores reflect more severe depressive symptoms.BAI (25): This is a self-report tool for assessing the severity of anxiety symptoms. It comprises 21 items focusing on physiological and emotional symptoms, for example, palpitations, trembling, feelings of nervousness. Each item is scored from 0 to 3, with total scores ranging from 0 to 63. Higher scores indicate more severe anxiety levels.sEMG: Measurements included the root mean square (RMS) values of the bilateral erector spinae and bilateral multifidus muscles; amplitude-frequency changes; negative slope changes in median frequency; and bilateral differences in RMS values or activation timing. sEMG electrodes were placed over the bilateral erector spinae (approximately 2–3 cm lateral to the L1 and L3 vertebral levels) and the bilateral multifidus (at the L5 level). sEMG signals were recorded continuously and synchronously throughout the execution of a full prone trunk extension held test by the participants. The acquired sEMG RMS values quantified the level of muscle activation. Analyzed time-domain indices primarily included the mean amplitude of the electromyographic signal, reflecting the trend of muscle activation intensity throughout the test. Frequency-domain indices, such as the median frequency, were used to quantify the rate of muscle fatigue during sustained contraction. Bilateral differences in RMS values or activation timing were analyzed to assess disordered muscle activation sequences or compensatory patterns in patients with low back pain (see Figure 2).MSK US: Measurements included muscle thickness and cross-sectional area of the bilateral erector spinae and multifidus; shear wave elastography; and muscle echogenicity and homogeneity. MSK US was used to assess the bilateral multifidus and bilateral erector spinae. Images were acquired at three times: before, during, and after the participant performed the prone trunk extension hold test. In the resting state, participants lay prone in a completely relaxed position. Transverse images at the L4-L5 level were used to measure the thickness and cross-sectional area of the multifidus muscle and the bilateral erector spinae muscle. Shear wave elastography was employed to obtain elasticity modulus values or shear wave speeds to quantify muscle stiffness. During the maintenance phase of the test movement at 30 and 60 s, a brief pause allowed for rapid acquisition of images depicting muscle morphology and elasticity during isometric contraction. Muscle echogenicity and homogeneity will be objectively quantified using grayscale histogram analysis. Immediately following the test, resting state parameters were measured again to assess the impact of acute fatigue on muscle status. Probe positioning and skin markings were kept consistent for all measurements to ensure data comparability (see Figure 4).Medication usage: The weekly frequency and usage dosage of medication during the study period were recorded for both the control and treatment groups. These data will be quantitatively analyzed to evaluate the medication use of Tuina intervention.

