
**Figure 4 fig4:**
[figure not shown]
Examples of sEMG and MSK US inspection operations. **(A)** Examples of sEMG inspection operations. **(B)** Examples of MSK US inspection operations.

The VAS is assessed prior to the first treatment and after each subsequent treatment session. Medication usage was evaluated before the initial treatment and after the second, third, and fourth weeks of treatment. The ODI, SF-36, BDI-II, BAI, sEMG, and MSK US assessments were performed for patients with chronic nonspecific low back pain prior to the first treatment and upon completion of the treatment phase. Additionally, follow-up evaluations were conducted at 4, 8, and 12 weeks after the conclusion of the treatment intervention, primarily collecting data on patients’ pain VAS, ODI, and medication usage during clinical visits (see Table 2).

**Table 2 tab2:** The schedule of enrollment, interventions, and assessment.

Visit item	Enrollment	Allocation	Treatment period					Follow-up period		
Time point	−3–0 day	0 day	1 day	1 week	2 week	3 week	4 week	8 week	12 week	16 Week
Register	✓									
Sign the informed consent form		✓								
General information		✓								
Inclusion and exclusion criteria		✓								
Randomization		✓								
Basic information, current medical history, past medical history		✓								
Intervation										
Tuina combined with Loxoprofen Sodium patches										
Loxoprofen Sodium patches										
Assessments										
VAS		✓	✓	✓	✓	✓	√	√	√	√
ODI		✓					√	√	√	√
SF-36		✓					√			
sEMG		✓					√			
BDI-II		✓					√			
BAI		✓					√			
MSK-US		✓					√			
Medication usage		✓		✓	✓	✓	√	√	√	√
Safety evaluation										
Adverse events										

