### Adverse events

In this study, the monitoring, assessment, and management of adverse events related to Tuina followed a comprehensive standard operating procedure. Initially, any discomfort reported during the intervention period was promptly evaluated and judged by at least two clinical experts with senior professional titles from our research group. According to previous literature and clinical consensus, common adverse events associated with Tuina manipulation primarily include worsening local pain or discomfort, skin redness or ecchymosis, transient muscle soreness, and, in rare instances, temporary dizziness or fatigue; the adverse reactions associated with Loxoprofen Sodium patches, including gastrointestinal discomfort, contact dermatitis, and erythema at the application site. Upon confirmation of any adverse event, a detailed record was made, and the event was reported to the study’s ethics committee within 24 h.

Management was implemented based on the severity of the event using a graded approach: For mild local discomfort, participants could continue in the study under close observation. For moderate pain exacerbation or persistent dizziness, the current treatment cycle was immediately suspended, and symptomatic treatment was provided until complete symptom resolution and safety were confirmed through evaluation. In the event of a serious adverse event, the research intervention for that subject was immediately and permanently terminated, emergency procedures were initiated, and reports were submitted to the relevant authorities within the mandated timeframe. Furthermore, if prohibited concomitant treatments, such as the systemic use of other analgesic medications or receiving other physical therapies, were used to manage an adverse event, or if the event led to the subject being unable to complete follow-up for primary outcome measures, including pain scores, functional disability indices, and surface electromyography assessments, the data from lost-to-follow-up participants will be supplemented using multiple imputation and included in the final efficacy analysis. Their safety data were retained and reported.

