### Statistical analysis

Statistical analysis will follow the ITT principle, including all randomly assigned participants. Data from all lost-to-follow-up participants will be completed using multiple imputation, and statistical analysis will be conducted using SPSS 26.0 software. All continuous variables will be first tested for normality. Normally distributed data were presented as mean ± SD, and t-tests were performed for statistical analysis; while non-normally distributed data will be presented as M (P25, P75), and statistical analysis was performed using the Mann–Whitney U test. Categorical variables will be expressed as frequencies or percentages, and statistical analysis was performed using the chi-square test. The longitudinal analysis will be performed using a linear mixed model with baseline value as covariate. A two-sided *p*-value of <0.05 will be considered statistically significant. To address the problem of multiple Type I errors, the Bonferroni correction method will be used to adjust the significance level.

For safety analysis, the number of cases with abnormal changes in laboratory indicators will be described, and the incidence, presentation, severity, and correlation with the intervention will be reported in detail for all adverse events.

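### The planned laboratory safety analysis has no scheduled measurement behind it, and equal recording of adverse events in the two arms is not assured

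*Protocol article*

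**What the plan says.** **Safety analysis.** The Statistical analysis section makes two commitments. On laboratory data, "the number of cases with abnormal changes in laboratory indicators will be described". On adverse events, "the incidence, presentation, severity, and correlation with the intervention will be reported in detail for all adverse events". Both are descriptive; the paragraph names no between-arm test.

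**What is measured.** The primary outcome is VAS pain. For the rest, "Secondary outcome measures included ODI questionnaire, SF-36, BDI-II, BAI, sEMG, MSK US, and medication usage". Table 2 ("The schedule of enrollment, interventions, and assessment") sets out the visits item by item, in one schedule for both arms. It has rows for safety evaluation and adverse events but none for laboratory tests. The exclusion criteria give the only other mention of laboratory work, where certain secondary causes of back pain are "confirmed by relevant laboratory and imaging examinations".

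**How adverse events arise.** The Adverse events section opens by saying that "the monitoring, assessment, and management of adverse events related to Tuina followed a comprehensive standard operating procedure". It then says that "any discomfort reported during the intervention period was promptly evaluated". The same paragraph also lists expected reactions to the patch.

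**Contacts.** For the experimental group, "The intervention is administered three times weekly, with each session lasting 30 min", over 4 weeks. The Control group section describes patch use as needed and a medication record form, with no treatment sessions. Table 2 marks VAS and medication usage for both arms at weeks 1 to 4 and at weeks 8, 12 and 16.

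**The concern.** There are two separate issues.

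1. A change in a laboratory value needs a baseline value and a later one. The analysis section promises a count of such changes, yet the schedule shows no occasion on which the later value is obtained. Anyone following the article would have nothing to report, or might report zero cases when nobody was tested.

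2. The described trigger is a report of discomfort, and the article does not say on which occasions patients are asked. One arm sees a clinician three times a week for four weeks and the other does not. If reports come up mainly at contacts, a mild event has more chances of being recorded in the Tuina arm. The Objective in the abstract names safety beside effectiveness, and incidence is to be reported. A descriptive incidence is distorted by unequal recording just as a tested one is.

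**Working it through.** **Laboratory data.** The places where a source could stand are:

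- Secondary outcomes: no laboratory measure.
- Assessment text and Table 2: no laboratory row. This is an absent row, not a row whose marks are missing.
- Adverse events: no laboratory test.
- Exclusion criteria: laboratory examinations used to confirm an exclusion, with no repeat stated.

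No place gives a post-baseline value, so no change can be computed.

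**Contacts in weeks 1 to 4.** The article gives no figure for safety ascertainment to reproduce, so the counts are built from its schedule.

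- Tuina sessions: 3 per week × 4 weeks = 12, or 12 × 30 min = 6 hours.
- Shared assessments, from Table 2: weeks 1, 2, 3 and 4 = 4 in each arm.
- Experimental: 12 + 4 = 16. Control: 0 + 4 = 4.
- If the weekly assessment takes place at a Tuina session, the count is 12 against 4.

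**Possible size.** The documents give no chance of an event being picked up at a contact, so it is an assumption, q, and a range is shown. The model takes equal true risk in both arms, an event that persists through all contacts, the same q at each contact, and no reports between contacts.

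Share of existing events recorded after k contacts = 1 − (1 − q)^k

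Apparent ratio = [1 − (1 − q)^k for experimental] / [1 − (1 − q)^k for control]

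Worked case, q = 0.05: control 1 − 0.95^4 = 0.185; experimental 1 − 0.95^16 = 0.560; ratio 0.560 / 0.185 = 3.0.

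| q (assumed) | Control, 4 contacts | Experimental, 16 contacts | Ratio, 16 vs 4 | Ratio, 12 vs 4 |
|---|---|---|---|---|
| 0.05 | 0.185 | 0.560 | 3.0 | 2.5 |
| 0.10 | 0.344 | 0.815 | 2.37 | 2.09 |
| 0.20 | 0.590 | 0.972 | 1.65 | 1.58 |
| 0.30 | 0.760 | 0.997 | 1.31 | 1.30 |
| 0.50 | 0.938 | 1.000 | 1.07 | 1.07 |
| 0.80 | 0.998 | 1.000 | 1.00 | 1.00 |

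The middle columns are shares of existing events, not of patients. In patient counts, with an assumed true risk of 20% in both arms, 40 × 0.20 = 8 patients per arm have an event. At q = 0.10 and 16 against 4 contacts, 8 × 0.815 = 6.5 and 8 × 0.344 = 2.8 would be recorded. At q = 0.50 the figures are 8.0 and 7.5.

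**The case against.** On laboratory data there is little to set against the point. One may say that it is minor, because no effectiveness result depends on it, and that with no tests there would be nothing to report rather than a misleading result. The first is fair. The second depends on how the report is written. Neither gives the sentence a data source.

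On adverse events the opposing case is stronger:

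- The capture rule refers to the intervention period, a 4-week window common to both arms, and not to sessions.
- The Adverse events section lists patch reactions, and the analysis covers all adverse events.
- Table 2 has an adverse-event row that is not split by arm. It shows no marks in the text available, but the two intervention rows are blank as well, so marks were probably lost in extraction. The blank row is no evidence that events are not asked about.
- The Interventions section says that treating staff record attendance and collect no other trial data, which may limit capture at sessions.
- The method of asking may stand in the operating procedure to which the article refers, which is not shown.
- No between-arm test of safety is planned.

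These points stand, and they limit the claim. A reader might infer from 12 sessions against none that the arms' adverse-event rates cannot be compared, or that control-arm reactions are in fact under-detected. The documents support neither. Control patients have four shared assessments during treatment and three afterwards, and the distortion disappears if events are asked about well at those visits. What remains is that the article states a report-based trigger, frames it around Tuina, and gives one arm several times as many contacts. The follow-up text names VAS, ODI and medication usage as the main data collected and does not mention adverse events.

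**Conclusion.** The laboratory point holds in full: the analysis stated in the article has no measurement in its own schedule. That rests on the printed text alone and needs no assumption.

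The adverse-event point holds in a limited form: equal ascertainment is not assured. Contacts in weeks 1 to 4 are about 16 against 4. Under equal true risk, the apparent experimental-to-control ratio could lie anywhere from about 3.0 (5% pick-up per contact) to 1.0 (80%). The pick-up probability, the persistence of events and the absence of reports between contacts are all assumptions, so the range shows what is possible and does not estimate the bias. Under these assumptions any distortion would make the Tuina arm look worse.

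The primary outcome and the sample size are not affected. The change is worth making because safety is a stated objective and events never asked about cannot be recovered later.

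**What to change.** 1. Delete the laboratory sentence from the safety analysis. If tests are in fact repeated after baseline, name them and add their visits to Table 2.
2. State that the same adverse-event question, covering both Tuina and patch reactions, is asked in both arms at the shared visits at weeks 1, 2, 3, 4, 8, 12 and 16.
3. Describe between-arm incidence from those visits only, and report events noted only at Tuina sessions separately, so that none is lost.

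The cost is a wording change and a short checklist at visits that already take place. Fewer events enter the between-arm description. The Trial status section reports 9 of the planned 80 participants enrolled at submission, so most patients could still be followed under the common question. The date of the change should be recorded so that participants enrolled before it can be identified.

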### Trial status

The trial is currently in the participant recruitment phase. Following trial registration, the first participant was enrolled on October 1, 2025. Recruitment is expected to be completed by June 30, 2027. As of the submission date of this protocol manuscript, a total of 9 participants have been successfully enrolled. We hereby declare that no interim data analysis has been performed, the database remains open and unlocked, and all researchers and statisticians are completely blinded to the accumulated outcome data at the time of submission.

## Discussion

CNLBP represents a persistent individual burden and is a significant contributor to socioeconomic costs. Tuina, one of the most commonly utilized complementary therapies, and nonsteroidal anti-inflammatory drugs (NSAIDs), a core intervention recommended in clinical guidelines, are both treatment modalities for CNLBP. While non-pharmacological treatments are often preferred, and numerous studies have confirmed the benefits of NSAIDs (26), research directly comparing these two approaches to guide individualized treatment for specific patient populations remains scarce.

In clinical practice, many patients with CNLBP seek physical therapies such as Tuina, either alongside or instead of pharmacological treatment. Existing clinical guidelines frequently position medication as a foundational approach, while Tuina is also a widely applied intervention. Numerous studies have separately confirmed the efficacy of medication and Tuina. However, there is a notable lack of research rigorously comparing combination therapy (Tuina plus medication) against medication alone. Such comparative studies hold significant practical value for guiding individualized clinical treatment choices. This study introduces the use of specialized Tuina gloves to standardize the manipulation technique, directly addressing the critical challenge of achieving uniformity and reproducibility in clinical Tuina practice.

Given that the core clinical issues in CNLBP are pain and functional limitation, and to clearly elucidate the differences in efficacy between the two treatment protocols, this study designates pain intensity as the sole primary outcome (VAS), and muscle function represents an objective secondary outcome. This approach allows for a comprehensive evaluation encompassing both the patient’s subjective experience and the objective improvement in physical function. Furthermore, the study will delve into the specific changes in muscle function following Tuina intervention, aiming to provide evidence-based insights into the potential mechanisms underlying its therapeutic effect in CNLBP.

This study has certain limitations. First, due to the open-label nature of Tuina, blinding of patients and therapists is not feasible. Additionally, this single-center trial is conducted at a TCM-affiliated hospital and lacks an attention-matched control group, where enrolled patients likely have a high baseline preference for Tuina, which may amplify expectation bias and placebo effects in the experimental group. Therefore, our findings may not be fully generalizable to populations or settings with lower familiarity with TCM manual therapy. Although outcome assessors and data analysts are blinded to minimize bias in objective biomechanical data, this does not reduce measurement bias for the primary outcome (VAS). Second, constrained by the follow-up duration, a 12-week observation period may be insufficient to fully capture the long-term effects of the treatment regimen for a chronic condition such as CNLBP. Therefore, further studies with longer follow-up are necessary to validate the long-term differences between medication alone and Tuina combined with medication. Third, the two-arm design lacks a Tuina-alone control and a step-up phase. Thus, any observed benefit of combination therapy may arise from Tuina alone or non-specific effects rather than true synergy. Future trials should address these limitations using three-arm, run-in, and sham-controlled designs. Fourth, the inclusion age is capped at 60 years to reduce confounding from age-related degenerative pathologies. Consequently, our findings may not be generalizable to geriatric patients.

This study aims to clarify the clinical effectiveness of combining Tuina with medication for treating CNLBP. The findings are expected to provide a scientific reference to inform clinical decision-making regarding comprehensive treatment strategies for this condition.
